### Quality control

The trial protocol has been reviewed and revised by experts on acupuncture, neurology, rehabilitation, statistics, and methodology several times. Before the trial, all staff are required to attend a series of training sessions. These sessions will ensure that the personnel involved fully understand the research protocol and standard operating procedures for the study. During the trial supervisors will check on case reports and acupuncture operation twice per month. The research team will meet regularly (once every three months) throughout the trial to discuss progress, including recruitment, withdrawals, treatment compliance, and adverse events. Economic compensation and health education are also considered as methods for improving compliance. A Data and Safety Monitoring Board was set up on 10 May 2012 to monitor the performance and safety of the trial.

### Sample size calculation

The primary efficacy parameter is the change in NIHSS scores from baseline to the end of treatment after three weeks. According to our preliminary test and previous study
[26], the decrease in NIHSS score was conservatively estimated to be 5 in the acupuncture group and 3 in the control group, with a standard deviation of 5.0. A two-sided 5% significance level and 80% power were considered, and the following equation was used:

(1)n=2za2+zβ2σ2Δ2

Approximately 100 participants in each group were calculated to be required. Estimating a 20% dropout rate, each group will require 125 initial participants.

### Statistical analysis

All data will be analyzed by a blinded statistician using the SPSS(Statistical Product and Service Solutions) statistical package program (version 17.0, SPSS Inc., Chicago, Illinois, United States) at a separate location from the clinical research institute of Zhejiang Provincial Hospital of Chinese medicine. Baseline data will be collected and compared first. All patients randomized to each group are included in the analysis and the data analysis will be conducted using two-sided significance tests at the 5% significance level. The analysis of swallowing disorder and cognitive impairment will be made on the defined population of corresponding dysfunction in the baseline assessment. Different statistics are presented differently; for example, continuous variables will be expressed as mean ± SD, *t*-test will be used for comparisons of two independent samples, and non-parametric tests will be used for variables that do not follow a normal distribution. A *P* value of less than 0.05 (α value of 0.05) is considered to indicate statistical significance. A safety analysis will be performed by analyzing the frequency of adverse events suspected as related to the treatment. The data for adverse events are collected through the symptoms reported by the patients, and observations by a researcher at every visit.

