## Discussion

Acupuncture is widely accepted by Chinese people and it is increasingly requested by patients and their relatives in Western countries. Stroke is one of the most common diseases for which acupuncture treatment is recommended, according to the World Health Organization
[27]. However, Cochrane reviews have shown that although acupuncture appeared to be safe, there is no clear evidence of benefit. The number of patients in existing trials is too small to be certain whether acupuncture is effective for the treatment of acute ischemic stroke. Larger, methodologically sound trials are required
[16,28].

For clinical trials blinding is difficult for acupuncture so real randomized placebo-controlled trials seem impossible. In Western medical hospitals in China, acupuncture is used less for stroke compared with Chinese medical hospitals, so setting up a no acupuncture control is feasible. We will conduct our trial in three Western medicine hospitals to ensure a sufficient source of subjects and compliance of the control group. Because many stroke patients will ask for traditional Chinese medicine and acupuncture treatment during the recovery period, we have set the follow-up period as only four weeks.

Under strict quality control, this study could potentially confirm whether or not acupuncture (including scalp acupuncture and electroacupuncture) is an effective adjunct to the standard rehabilitation therapy for acute stroke. Our study may also confirm if acupuncture can be effective in promoting the recovery of motor function and is beneficial to swallowing disorder and cognitive impairment.

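### The named t-test on three-week NIHSS change cannot include patients without a three-week score, so it does not deliver the promised analysis of all randomised patients

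*Protocol article*

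**What the plan says.** The Statistical analysis section of the protocol article sets the population: "All patients randomized to each group are included in the analysis". For continuous variables it offers, by way of example, the t-test for two independent samples, with non-parametric tests where the distribution is not normal. It names no other method for continuous outcomes.

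The Sample size calculation section is the only place that fixes a single primary time point: "The primary efficacy parameter is the change in NIHSS scores from baseline to the end of treatment after three weeks". It then states "Approximately 100 participants in each group were calculated to be required" and "Estimating a 20% dropout rate, each group will require 125 initial participants".

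Under Outcome assessment and Primary outcome measurement, NIHSS is scheduled at baseline, at one week, at three weeks and at a later follow-up. Every patient still in the trial after one week of treatment should therefore have a post-baseline score before the primary time point.

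**The concern.** A change from baseline to three weeks exists only for a patient with a three-week score. A two-sample test on that change compares the patients who have one. The article promises everyone randomised, allows for a fifth dropping out, and names a test that has no place for a patient without the endpoint. It does not connect the three.

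Two things are at stake. First, a result labelled as covering all randomised patients could in fact cover only those seen at three weeks. Patients know whether they receive acupuncture, so loss that differs by arm is possible, and a comparison of completers is then no longer protected by randomisation. Second, the week-one scores of patients lost later carry information about their recovery, and the named test makes no use of them.

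**Working it through.** **Inputs, all from the Sample size calculation section.** Mean decreases: "the decrease in NIHSS score was conservatively estimated to be 5 in the acupuncture group and 3 in the control group", so the difference is Δ = 2. Spread: "with a standard deviation of 5.0". Error rates: "A two-sided 5% significance level and 80% power were considered". Dropout is 20%, with 125 per arm and 250 in total.

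**1. The plan's own figure.** n = 2(z₀.₉₇₅ + z₀.₈₀)²σ²/Δ² = 2 × (1.960 + 0.842)² × 25/4 = 98.1, so 99 per arm. The article rounds to about 100. Inflation gives 100/(1 − 0.20) = 125. Both figures reproduce.

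**2. What the sizing assumes about dropouts.** Power by the normal approximation (exact t in brackets):
- 100 per arm with outcomes: 80.7% (80.4%)
- 125 per arm with outcomes: 88.5% (88.3%)

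The stated 80% is therefore the power with about 100 scores per arm. The 125 − 100 = 25 expected dropouts per arm, 50 of 250, are counted as adding nothing. That is a cautious way to size a trial. It is not a description of an analysis in which all 250 contribute.

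**3. Who can enter the named test.**
- Patient with a three-week score: enters.
- Patient with a week-one score only: has no three-week change, does not enter, and the week-one score is unused.
- Patient with baseline only: does not enter.

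The last two groups can enter only if a three-week value is supplied for them, and the article states no rule for that. The choice of rule matters. For example, suppose 20% in each arm are assigned zero change and the completers have means 5 and 3 with SD 5:
- The expected difference is 0.8 × 2 = 1.6.
- The SDs are √(0.8 × 50 − 4²) = 4.90 and √(0.8 × 34 − 2.4²) = 4.63.
- Power with 125 per arm is 75.6%.

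**4. Possible bias if only patients with a three-week score are compared.** Let d be the share dropping out and g the mean improvement of dropouts minus that of completers, with A for acupuncture and C for control. The mean of all randomised patients in an arm is the completer mean plus d × g. Hence, for acupuncture minus control,

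bias = d_C g_C − d_A g_A.

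The values of d and g below are assumptions, and the article gives none by arm. Type I error is for no true difference, with standard error 5√[1/(125(1 − d_A)) + 1/(125(1 − d_C))].

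| d_A / d_C | g_A / g_C (points) | Bias (points) | Two-sided type I error |
|---|---|---|---|
| 20% / 20% | −5 / −5 | 0 | 5.0% |
| 20% / 20% | −3 / 0 | +0.6 | 13.6% |
| 20% / 20% | −5 / 0 | +1.0 | 29.3% |
| 20% / 20% | 0 / −5 | −1.0 | 29.3% |
| 25% / 15% | −2 / −2 | +0.2 | 5.9% |
| 25% / 15% | −5 / −5 | +0.5 | 10.9% |
| 15% / 25% | −5 / −5 | −0.5 | 10.9% |

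A positive sign favours acupuncture. If poor responders leave the control arm in greater numbers (rows four and seven), the bias runs against acupuncture.

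**The case against.** The strongest reply is that this is only silence about missing data, which an article may leave to a statistical analysis plan or full protocol, and neither is shown. That stands for the bare missing-data rule: its absence here is not the point. What remains is that the article does commit itself to a population and a type of test, and that a better test is available on data it already plans to collect.

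Several stronger readings are tempting, and the article does not support them:
- **That the statements contradict each other.** Enlarging enrolment for dropout while analysing patients as randomised is ordinary practice, and a t-test can follow imputation.
- **That the plan deletes up to 50 patients.** Nowhere does it say so. It gives a dropout rate without defining dropout as having no NIHSS score, it does not use the term intention-to-treat, and it introduces the t-test as an example.
- **That controls are expected to be hard to retain.** The Discussion says Western-medicine hospitals were chosen "to ensure a sufficient source of subjects and compliance of the control group". That passage is about controls obtaining acupuncture and about compliance, and it describes a safeguard. Treatment is given during the inpatient stay, and the sizing endpoint falls at the end of it, which also helps follow-up.
- **That the trial is biased towards acupuncture.** No figure in the article shows dropout that differs by arm or relates to outcome, and the direction in the table turns with the assumption.

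It is also fair to say that a mixed model does not cure dropout that depends on unobserved scores. That stands, and it is the reason for the sensitivity analysis.

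**Conclusion.** The point holds in a limited form. As written, the named test on three-week NIHSS change includes only patients with a three-week score, so by itself it does not deliver the promised all-randomised analysis. At the planned dropout rate this could concern about 25 patients per arm, if dropout means no three-week score. The week-one scores of those patients would go unused.

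Bias is a possibility and not a demonstrated fault. It is zero when dropout and its reasons are alike in both arms. It is 0.2 to 1.0 NIHSS points in size, in either direction, under the assumed unequal patterns, compared with a target difference of 2. The sample size is not wrong and needs no change.

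**What to change.** Replace the t-test as the primary analysis with a mixed model for repeated measures on all scheduled post-baseline NIHSS scores. Include treatment by visit, baseline NIHSS and centre, and take the treatment contrast at three weeks as the primary test. A patient seen at week one but not at week three then contributes in the assigned arm.

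Describe the population as randomised patients with at least one post-baseline NIHSS score, analysed in the arm assigned, and report by arm how many have none.

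Add one delta-adjusted sensitivity analysis in which missing three-week scores are imputed and shifted by a stated range, separately by arm. It is needed because the model assumes data missing at random, and because patients with no post-baseline score still contribute nothing to it. Fix these choices before the group codes are opened.

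The cost is a change of wording, slightly more programming and reliance on the missing-at-random assumption. No extra visits or patients are needed. Baseline adjustment should also gain some precision. The article gives no baseline-to-outcome correlation from which to size that gain.

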### Inclusion criteria

We will choose patients aged between 35 and 80-years-old who are hospitalized with acute ischemic stroke according to the criteria of both Western medicine and traditional Chinese medicine. The stroke onset must be between two to seven days beforehand, with a National Institutes of Health Stroke Scale (NIHSS) score of between 4 and 24. The stroke should be the first incidence or patients can have a history of stroke but without disability (modified Rankin Scale, mRS score ≤1).

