### Randomization and blinding

Randomization to acupuncture or no acupuncture will be computer-generated by independent research staff using software. The treatment codes are placed in sealed opaque envelopes which will be distributed by research nurses who will be trained before the trial and will not participate in treatment or nursing. Patients in this research will be told that they will receive routine rehabilitation treatment with or without acupuncture. It is impossible to blind the acupuncturists because they must be trained to perform the acupuncture according to the research plan. A special rehabilitation doctor from each center will be assigned to be the assessor who is blinded to the patient treatment group and does not participate in the treatment of subjects. All study personnel including the rehabilitation therapists, outcome assessors, and data analysts will be blinded to group assignments.

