#### Baseline assessments

Baseline assessments will be conducted before randomization, including gender and age of patients, clinical syndrome (left or right hemiplegia), diseased location and size, NIHSS and Fugl-Meyer assessment (FMA) scores, cognitive impairment based on the Montreal cognitive assessment (MoCA), and swallowing disorder according to the standardized swallowing assessment.

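### The primary NIHSS change is planned as an unadjusted two-sample test with a distribution-driven switch: valid, but it leaves baseline NIHSS unused and the reported effect measure open

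*Protocol article*

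**What the plan says.** The Sample size calculation section defines the primary parameter: "The primary efficacy parameter is the change in NIHSS scores from baseline to the end of treatment after three weeks". It assumes that "the decrease in NIHSS score was conservatively estimated to be 5 in the acupuncture group and 3 in the control group". The SD of the change is taken as 5.0, and the error rates are given as follows: "A two-sided 5% significance level and 80% power were considered". This leads to about 100 evaluable and 125 randomized patients per group.

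The Statistical analysis section then gives one approach for continuous variables, a t-test that "will be used for comparisons of two independent samples, and non-parametric tests will be used for variables that do not follow a normal distribution". The sentence is introduced as an example and does not name NIHSS, but no other method for a continuous outcome appears in the article. Baseline data are to be compared between groups; nothing is said about using them in the outcome analysis.

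Baseline severity is available. Patients enter "with a National Institutes of Health Stroke Scale (NIHSS) score of between 4 and 24", and the assessments made before randomization include "NIHSS and Fugl-Meyer assessment (FMA) scores". The Primary outcome measurement section says the scale starts at 0 and describes NIHSS as a strong predictor of recovery. Each of the three centres has its own blinded assessor: "A special rehabilitation doctor from each center will be assigned to be the assessor".

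**The concern.** Subtracting the baseline value does not make a change score independent of baseline. Here a link is built in. A patient who enters at 4 can fall by at most 4 points, while one who enters at 24 has room for a much larger fall. If change still depends on baseline, a comparison that ignores baseline has two costs. Variation that baseline could explain stays in the error term. A chance difference in baseline severity between the arms also carries into the estimated effect, and the planned baseline comparison would show such a difference without any stated way of dealing with it.

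The second issue is the switch. The article gives no criterion for judging normality, so the form of the primary result is settled by the observed data. If the switch happens, a rank-type comparison replaces the mean difference in change on which the sample size rests, and the article does not say which effect measure would then be reported.

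**Working it through.** **Inputs from the article.** Difference 5 − 3 = 2 points; SD of change 5.0; two-sided 5% level; 80% power; about 100 evaluable per group; 20% dropout; baseline NIHSS 4 to 24; scale minimum 0. **Inputs not in the article, so assumed:** the correlation ρ between baseline and three-week NIHSS, and the ratio k of follow-up SD to baseline SD.

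**1. The article's own figure.** n = 2(z_α/2 + z_β)²σ²/Δ² = 2 × (1.960 + 0.842)² × 25/4 = 98.1, rounded up to 99 per group, against about 100 stated. With dropout, 100/(1 − 0.2) = 125, as stated. At 100 per group the standard error of the unadjusted difference is 5√(2/100) = 0.707. The non-centrality is 2/0.707 = 2.83, and exact t-test power is 80.4%. The sample size agrees with the unadjusted test.

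**2. Precision with baseline in the model.** Let s₀ be the baseline SD and s₁ = k·s₀ the follow-up SD. Fixing the change SD at 5.0 gives s₀²(1 + k² − 2kρ) = 25. The ANCOVA residual variance is s₁²(1 − ρ²), so its ratio to 25 is k²(1 − ρ²)/(1 + k² − 2kρ). For k = 1 this reduces to (1 + ρ)/2.

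| k | ρ | variance ratio | residual SD | power at 100 per group |
|---|---|---|---|---|
| 1.0 | 0.3 | 0.650 | 4.03 | 93.7% |
| 1.0 | 0.5 | 0.750 | 4.33 | 90.1% |
| 1.0 | 0.8 | 0.900 | 4.74 | 84.3% |
| 1.0 | 0.9 | 0.950 | 4.87 | 82.3% |
| 1.2 | 0.3 | 0.762 | 4.36 | 89.7% |
| 1.2 | 0.7 | 0.966 | 4.92 | 81.7% |
| 1.2 | 0.8 | 0.997 | 4.99 | 80.5% |
| 1.2 | 0.9 | 0.977 | 4.94 | 81.3% |

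For example, at k = 1.2 and ρ = 0.8 the ratio is 1.44 × 0.36/(2.44 − 1.92) = 0.518/0.520 = 0.997, so almost nothing is gained. The ratio also equals 1 − r², where r is the correlation of baseline with change. It therefore cannot exceed 1, and the only price of adjustment is one degree of freedom. The row k = 1.0, ρ = 0.9 is shown for completeness only. It implies s₀ = 5/√0.2 = 11.2, and a variable confined to 4 to 24 cannot have an SD above 10. Neither end of the 80% to 94% range depends on that row.

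**3. Chance imbalance.** Assume a baseline SD of 4 to 6. The 95% limit of the baseline mean difference at 100 per group is 1.96 × s₀ × √(2/100), which is 1.1 points for s₀ = 4 and 1.7 for s₀ = 6. The slope of change on baseline has size r × 5/s₀. An imbalance at the limit therefore shifts the unadjusted effect by r × 5 × 1.96 × √(2/100) = 1.386r, and the baseline SD cancels. This is 0.28 points at r = 0.2 and 0.69 points at r = 0.5, or 14% to 35% of the planned 2 points.

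**4. The switch.** The sample size section sets the target as a difference in mean change. The analysis section makes that target conditional on normality and gives no criterion. This needs no arithmetic: the two sections agree only if the data pass a check that is not defined.

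**5. Centre.** With one assessor per centre, a constant offset b in that assessor's scoring gives (Y₁ + b) − (Y₀ + b) = Y₁ − Y₀, so it drops out of the change score. Only centre differences in recovery, or drift in an assessor's scoring between visits, could remain, and the article gives no figure for either.

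**The case against.** The strongest reply is that nothing here is invalid. The t-test keeps its type I error, the estimate is unbiased over randomizations, and the sample size fits the test. All of that stands. A reader might infer that the primary analysis is biased or the trial underpowered, but the article's own figures show neither.

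The gain is also assumption-bound. A change score already removes part of the baseline variation, and the statement that NIHSS predicts recovery fixes no correlation. That stands too, so the size must be given as a range whose lower end is practically zero.

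Several other inferences are tempting and not supported:

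- **Assessor differences inflate the error term.** A constant offset cancels in the change score, as shown above. The article also states no stratification by centre that would call for a centre term on design grounds.
- **The test will usually switch.** The article names no normality test. Illustrative simulations with an invented skew put the failure rate at 63% or 73%, but those figures reflect the simulator's choices. One simulation of the same kind gave a type I error of 5.3% both with the switch and with the t-test alone, and power of 77% against 78%. What remains is the unclear effect measure, not a damaged error rate. The analyst is also blinded and the rule is stated in advance, which limits choosing a test to suit the result.
- **The assumed effect is unattainable because a patient entering at 4 cannot fall by 5.** The 5 points are a group mean. The floor shows only that change is linked to baseline.

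Finally, the sentence is generic, and covariates are often left to an analysis plan that is not shown. This carries some weight for the absence of a covariate. It carries less for the named two-sample test and the switch, which the article does fix.

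**Conclusion.** The point holds as a recommended improvement, not as an error that invalidates the trial. The article commits continuous outcomes, and so the primary three-week NIHSS change, to an unadjusted comparison whose form depends on the observed distribution, although the main prognostic measure is on file before randomization.

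At 100 per arm and a change SD of 5.0, baseline adjustment takes power from 80% to between about 80% and 94%, for correlations of 0.3 to 0.9 and SD ratios of 1.0 to 1.2. It was not below the unadjusted test in any case examined. An unlucky baseline imbalance at its 95% limit would move the unadjusted estimate by 0.28 to 0.69 points if baseline and change correlate at 0.2 to 0.5. All these correlations and SD ratios are assumptions. The objection to the switch needs none of them. The benefit of a centre term cannot be calculated from the article and forms no part of the stated size.

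**What to change.** For the primary outcome, replace the generic sentence with a single pre-specified analysis: three-week NIHSS, or its change from baseline, analysed by ANCOVA with treatment and baseline NIHSS. With baseline in the model, both forms give the same treatment effect apart from sign. Report the adjusted mean difference with its 95% confidence interval whatever the distribution looks like, using robust or bootstrap standard errors if needed. Keep a rank test as a sensitivity analysis only. Treat FMA in the same way with baseline FMA. A centre term may be added to allow for differences in recovery between centres, but no stated gain should rest on it.

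The cost is wording: baseline NIHSS and FMA are already collected, and the 250 patients need not change. Timing matters, though. The article is dated 8 June 2014 and expects completion by the end of that month, so the change must be documented with a date before unblinding.

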## Abstract

**Background:**

Acupuncture has been widely used as a treatment for stroke in China for more than 3,000 years. However, previous research has not yet shown that acupuncture is effective as a stroke treatment. We report a protocol for a multicenter, randomized, controlled, and outcome assessor-blind trial to evaluate the efficacy and safety of acupuncture on acute ischemic stroke.

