**Methods/Design:**

In a prospective trial involving three hospitals in the Zhejiang Province (China) 250 patients with a recent (less than 1 week previous) episode of ischemic stroke will be included. Patients will be randomized into two groups: an acupuncture group given scalp acupuncture and electroacupuncture, and a control group given no acupuncture. Eighteen treatment sessions will be performed over a three-week period. The primary outcome will be measured by changes in the National Institutes of Health Stroke Scale score at the one, three, and four-week follow-up. Secondary outcome measures will be: 1) the Fugl-Meyer assessment scale for motor function; 2) the mini-mental state examination and Montreal cognitive assessment for cognitive function; 3) the video-fluoroscopic swallowing study for swallowing ability; and 4) the incidence of adverse events.

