#### Secondary outcome measures

**Fugl-Meyer Assessment (FMA) scale for motor function** The FMA was developed as the first quantitative evaluative instrument for measuring sensorimotor stroke recovery, which includes an assessment of the upper extremity (UE, 66 points) and lower extremity (LE, 34 points). The motor domain has well-established reliability and validity as an indicator of motor impairment severity across different stroke recovery time points
[20].

**The mini-mental state examination (MMSE) and Montreal cognitive assessment (MoCA) for cognitive function** The MMSE, first introduced by Folstein and colleagues in 1975
[21], has become a standard tool for cognitive assessment in the clinical setting. It is a 10-minute bedside measure of impaired thinking in undeveloped, uneducated, diseased, or very old populations. The summed score of the individual items indicates the current severity of cognitive impairment
[22]. However, there are many difficulties in detecting early dementia with the MMSE. Most individuals meet clinical criteria for mild cognitive impairment (MCI), but have scores above 26 on the MMSE, which is within the range for normal elderly individuals. To address this problem the MoCA was developed as a tool to screen patients who present with mild cognitive complaints and usually perform in the normal range on the MMSE
[23]. The MoCA is used as a screening tool for MCI in baseline assessment in our study.

**Video-fluoroscopic swallowing study (VFSS) for swallowing ability evaluation** The functional dysphagia scale is based on the VFSS in stroke patients, which is a sensitive and specific method for quantifying the severity of dysphagia
[24,25].

**Incidence of adverse events** The subjects will be requested to voluntarily report information about adverse events. All adverse events happening during the trial will be recorded, such as pallor, sweating or dizziness, fainting during acupuncture treatment, bleeding, local hematoma, unbearable prickling, retained needle after treatment, and continuous severe pain more than one hour after acupuncture. The researcher will confirm the occurrence of adverse events and record all details such as the date of occurrence, time, degree, measurement related to the treatment, and causal relationship with the treatment. Serious adverse events will be reported to the principal investigator immediately.

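### The stated safety analysis counts adverse events suspected to be treatment-related, which is narrower than the declared outcome (incidence of all adverse events) and asymmetric against a no-acupuncture control

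*Protocol article*

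**What the plan says.** Four statements in the protocol article bear on this.

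- **Aim** (Abstract, Background): the trial is meant "to evaluate the efficacy and safety of acupuncture on acute ischemic stroke".
- **Outcome** (Abstract, Methods/Design): the fourth secondary outcome is "the incidence of adverse events". The Secondary outcome measures section repeats it. Neither place limits it to related events.
- **Collection** (Secondary outcome measures): "All adverse events happening during the trial will be recorded". Ascertainment combines voluntary patient report with observation: "The data for adverse events are collected through the symptoms reported by the patients, and observations by a researcher at every visit" (Statistical analysis). Causal relationship is one of the details recorded for each event, and the task falls to an unspecified person: "The researcher will confirm the occurrence of adverse events and record all details such as the date of occurrence".
- **Analysis** (Statistical analysis): "A safety analysis will be performed by analyzing the frequency of adverse events suspected as related to the treatment". No other safety analysis is described, and no comparison of all events or of serious events by arm.

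The control arm has the same conventional rehabilitation and no acupuncture (No acupuncture treatment group). No sham procedure is described.

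**The concern.** The outcome declared and the outcome analysed are different quantities. The declared one is the proportion of patients with adverse events in each randomised arm. The analysed one is the frequency of events that have also passed a causality judgement made after randomisation. A randomised comparison is fair because the arms are treated alike apart from the intervention, and this filter is not applied alike. Whether an event can be blamed on acupuncture depends on whether acupuncture was given.

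The distortion can run in either direction. An excess of events in one arm disappears from the comparison if those events are judged unrelated. Conversely, two arms with the same overall rate can look different because attribution is easier in one of them. Safety is half of the stated aim, and the population is enrolled two to seven days after stroke, when events not obviously due to needling are to be expected.

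**Working it through.** **No stated figure is affected.** The only computed figure in the article is the sample size, and it reproduces. With a difference of 2, SD 5.0, two-sided 5% and 80% power, n = 2(1.96 + 0.84)² × 25 / 4 ≈ 98, or 99 with the t-distribution, against the article's figure of about 100. Dividing 100 by 0.8 for dropout gives 125 per arm. The 125 is used below.

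**Step 1: outcome against analysis.**

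| | Events included |
|---|---|
| Declared secondary outcome | All adverse events |
| Events recorded | All adverse events |
| Events in the stated safety analysis | Those suspected as related to the treatment |

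The third row is a subset of the first two, and membership depends on a judgement made after randomisation.

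**Step 2: the two readings of *the treatment*.** The article does not define the term.

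- *Acupuncture only.* Control patients receive none, so their events cannot qualify. Several listed examples fit this reading (fainting during a session, a retained needle, pain after needling).
- *Everything given, including rehabilitation.* Control events can qualify, but each event's inclusion still depends on attribution. An acupuncture patient has two candidate causes and a control patient has one. Knowledge of the arm can affect the judgement.

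The filter is asymmetric on either reading.

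**Step 3: illustration of a false difference.** All rates here are assumptions. Take the same true proportion p of patients with an event in both arms, a fraction a of acupuncture-arm events judged related, and no control events judged related (the first reading). The expected analysed count is 125 × p × a against 0. By Fisher's exact test, 5 versus 0 of 125 gives P = 0.060 and 6 versus 0 gives P = 0.029. Six or more related cases would therefore be declared significant at 5%. That probability is P(X ≥ 6) for X ~ Binomial(125, p × a).

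| p (both arms) | All-cause count per arm | a = 10% | a = 30% | a = 50% |
|---|---|---|---|---|
| 10% | 12.5 | 1.25 v 0; 0.002 | 3.75 v 0; 0.17 | 6.25 v 0; 0.60 |
| 20% | 25 | 2.5 v 0; 0.04 | 7.5 v 0; 0.77 | 12.5 v 0; 0.99 |
| 30% | 37.5 | 3.75 v 0; 0.17 | 11.25 v 0; 0.97 | 18.75 v 0; >0.99 |

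Each cell gives the expected related counts, then the probability of a significant result when the all-cause rates are equal. The range runs from negligible to near certain, according to how freely events are attributed.

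**Step 4: illustration of a hidden difference.** Assume serious events in 8% against 4%: 0.08 × 125 = 10 and 0.04 × 125 = 5. If all are judged unrelated, the stated analysis shows 0 versus 0. The all-cause comparison shows 10 versus 5. Its risk difference is 4 percentage points, with standard error √(0.08 × 0.92/125 + 0.04 × 0.96/125) = 0.030, a 95% CI of about −1.9 to 9.9 points, and Fisher P = 0.29.

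**The case against.** The best defence is that the safety sentence excludes nothing. It can be read as an addition to the unrestricted secondary outcome, and a table of all events by arm may sit in a full plan that is not shown. It is true that the sentence does not say *only*. But the article does more than leave the analysis open: it states one, and that one does not match its own outcome. This is a rule to correct, not detail left out.

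A second defence is oversight. Serious events go at once to the principal investigator, the team reviews adverse events every three months, and a Data and Safety Monitoring Board is in place. This protects patients during the trial. It does not define the between-arm result that will be reported.

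A third is precision. With 10 versus 5 serious events the corrected analysis would still be inconclusive (Step 4), and at those assumed rates Fisher's test has a power of only about 17%. That stands. The correction makes the estimate the right one, not a precise one.

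Three stronger readings are tempting, and the documents do not support them.

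- *The control count is bound to be zero.* This follows only if the treatment means acupuncture. The article also uses the word for both arms: the Acupuncture group section says treatment starts in both groups, and Randomization and blinding speaks of rehabilitation treatment with or without acupuncture.
- *The person judging causality must know the allocation.* No passage says so. Randomization and blinding states that study personnel are blinded, while acknowledging that acupuncturists cannot be. Whether the researcher who confirms events is among the blinded is not stated.
- *The acupuncture arm has 18 occasions to report events and the control arm none.* Both arms have rehabilitation six days a week, and events are also collected by a researcher at every visit. The 18 sessions come on top of frequent contact in both arms.

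**Conclusion.** The concern holds in this form: the one safety analysis stated is narrower than the declared secondary outcome and than the data collected, and its causality filter cannot act symmetrically between acupuncture and a no-acupuncture, no-sham control. Events judged unrelated do not enter the comparison, so the analysis does not estimate adverse-event incidence by randomised arm.

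The size cannot be fixed from the documents, which give no event or attribution rates. Under the assumptions in Step 3, the chance of a spurious significant difference runs from 0.002 to above 0.99. It also rests on the acupuncture-only reading and on Fisher's test being used, since the article names no test for adverse events. The mismatch between outcome and analysis depends on none of these assumptions. The primary efficacy analysis and the sample size are unaffected.

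**What to change.** Replace the safety sentence in the Statistical analysis section with wording to this effect:

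- All adverse events, and separately all serious adverse events, will be compared between the randomised arms as the number and proportion of patients with at least one event, regardless of judged causality, with the risk difference and its 95% confidence interval.
- Events judged related to acupuncture (needling events) will be reported separately and descriptively for the acupuncture arm.

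The change should be made before any results by arm are seen, so that it cannot look like a choice made on the data.

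The cost is small. All events and their causal assessment are already recorded, so no new data are needed. The report gains one table and shows more events than a related-only count would. Intervals for rare serious events will be wide at 125 per arm and should be presented as such: a non-significant difference will not show that the arms are equally safe.
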